### Power analysis and sample size

A minimum of 16 and a maximum of 24 participants will be enrolled and randomized into groups. To our knowledge, the effect of IMST on fasting glucose and/or insulin sensitivity in any population have not previously been reported, nor have effects of IMST on systolic BP and EDD in T2DM been specifically ascertained. Thus, for our power analysis we estimated a modest effect size of 0.40 with alpha set at 0.05 using a repeated measures ANOVA within-between framework. A sample size of 16-24 will have 85-96% power for any outcome with an effect size of ≥ 0.40.

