Recently, a novel, time-efficient respiratory exercise called Inspiratory Muscle Strength Training (IMST) was developed (16). IMST is distinct from other traditional forms of exercise due to its abbreviated training format (i.e., 5 minutes daily), and is performed using a hand-held device while seated or standing (16). With just six weeks of training (5 days/week), high resistance-IMST has been shown to lower systolic blood pressure (systolic BP) ~9 mmHg in normotensive and hypertensive adults (17). Furthermore, it has been shown to improve endothelium-dependent dilation (EDD) by 45% in older adults with elevated blood pressure (18). These vascular effects of IMST are believed to reduce the risks of CVD, the number one cause of death in people with T2DM (19). IMST is safe and well tolerated, with adherence rates >90% in diverse populations (18, 20), and thus presents a manageable introductory or adjunctive program for improving cardiometabolic health in T2DM patients who have difficulty maintaining a traditional exercise program. However, the effects of IMST on glycemic control and insulin sensitivity, as well as systolic BP and EDD are unknown in patients with T2DM.

Vascular endothelial function and metabolic function are closely linked (21). The vascular endothelium produces nitric oxide (NO), which is released in response to increased arterial wall shear stress (i.e., increased blood flow) (22). Among its various functions, NO enhances glucose uptake into cells and improves insulin sensitivity (23). T2DM is associated with impairments in endothelial function, including reduced NO production and increased vascular inflammation (24). High resistance-IMST is a potentially effective tool to combat T2DM-associated endothelial dysfunction, as it has been shown to increase NO bioavailability and reduce oxidative stress (18)— key adaptations that could improve metabolic health. The latter is especially significant given the link to metabolic syndrome, which encompasses insulin resistance, impaired glucose metabolism, and hypertension (25), and therefore, heightens the risks for cardiac event or stroke (25).

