The potential for IMST to elicit cardiometabolic adaptations in diabetic patients warrants assessment. Accordingly, we outline a plan to interrogate the effects of 6 weeks of high-resistance IMST on glycemia (fasting plasma glucose), insulin sensitivity/resistance (fasting serum insulin and Homeostasis Model Assessment [HOMA-IR; ratio of fasting insulin/glucose]), resting BP, and NO-mediated EDD in T2DM patients. Participants will be randomized into either high-resistance (experimental) or low-resistance (control) groups, and complete IMST at home 5 days/week for 6 weeks, with each session lasting ~5 minutes (26). Participants will perform at either high relative resistance (75% of maximal inspiratory pressure in cmH_2_O, (PI_max_)) or low relative resistance (15% of PI_max_) (26). As this is a blinded study, the 15% will ensure participants feel a resistance, but there are not consistent cardiovascular improvements established in previous studies (17, 27, 28).

We will study T2DM patients before and after 6 weeks of high-resistance IMST to test the hypotheses that (1) fasting plasma glucose will decrease, and insulin sensitivity will improve, (2) resting systolic BP will decrease, and (3) high-resistance IMST will improve EDD resulting in clinically-meaningful improvements (i.e., >1% unit change) (29). We will obtain consent to collect blood DNA for banking and plasma for quantitative proteomics analysis. This will allow us to investigate novel protein expression changes before and after IMST. Omic technologies, such as proteomics, provide powerful tools for identifying biomarkers and developing new treatments (30, 31). Our study aims to use quantitative proteomics analyses to identify potential associations and putative markers related to the effects of IMST, which remain largely unexplored. We anticipate observing changes in protein abundance associated with metabolic and cellular processes following IMST, particularly in relation to outcomes in T2DM. However, it is important to note that this exploratory experiment focused on associations rather than mechanisms.

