## Materials and methods

### Study design

The Diabetes Inspiratory Training (DIT) study is a randomized, sham-controlled, exploratory clinical trial examining the effects of IMST in 24 adults with T2DM. This is a 6-week intervention study design. An outline of the study is shown in **Figure 1**.

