### Statistical plan

Data will be analyzed with a repeated measures ANOVA test and Sidak *post hoc* testing using SPSS version 28.0. We will examine both group-by-sex and group-by-age interactions, and report effect sizes along with confidence intervals, in addition to p-values. All tests will be two-sided with alpha set at 0.05.

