## Discussion

Regular exercise is one of the most commonly prescribed non-pharmacological interventions for T2DM management and yields improvements in glycemic control and insulin action (6, 7). However, aerobic exercise is physically strenuous and time-consuming (10, 11) and less than half of T2DM adults participate in exercise on a regular basis. IIn contrast, IMST is a novel form of high intensity training that can be performed whether sitting or standing requires only 5 minutes per day, and rapidly improves blood pressure, endothelial vascular function, and vascular resistance among hypertensive adults (17, 18, 20, 28). Whether IMST can also affect changes in fasting blood glucose or insulin sensitivity is of critical interest and important for adults with T2DM, along with establishing if these blood pressure lowering effects and increased EDD are also seen in this population following IMST.

A study by Corrêa et al. studied the acute effects of IMST on glucose variability and showed significant improvements in glucose immediately following the training (42). Additionally, another study which was for 12 weeks at a lower resistance of 30% revealed no significant changes in blood glucose levels (43). The discrepancies across these findings are likely due to populations studied, the timeframe of the training and the resistance used. To our knowledge there have been no investigations that have reported the effects of chronic IMST training at a resistance of 75% or an interval training protocol similar to ours on glycemic control and insulin sensitivity in T2DM.

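### The 85–96% power stated for a modest effect of 0.40 in any outcome corresponds to a between-arm difference in change of 1.6 SD of change, which is very large

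*Protocol article*

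**What the plan says.** Under Power analysis and sample size, the protocol article says: "A minimum of 16 and a maximum of 24 participants will be enrolled and randomized into groups". It explains that the effects on glucose and insulin sensitivity have not been reported, nor those on systolic BP and EDD in T2DM. For that reason, "we estimated a modest effect size of 0.40 with alpha set at 0.05 using a repeated measures ANOVA within-between framework". It concludes: "A sample size of 16-24 will have 85-96% power for any outcome with an effect size of ≥ 0.40".

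The section does not say whether 0.40 is Cohen's f or a standardised mean difference. It gives no pre-post correlation and does not convert 0.40 into mg/dL, HOMA-IR units, mmHg or FMD units. The Statistical plan section names a repeated measures ANOVA and adds: "All tests will be two-sided with alpha set at 0.05".

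**The concern.** A reader who sees a modest effect size of 0.40 will probably think of a standardised difference of that order. A trial with 8 to 12 participants per arm cannot have 85–96% power for such a difference between arms. Either the power or the word *modest* has to give way.

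What is at stake is how a null result is read. If the trial is believed to have had at least 85% power for modest effects on any outcome, a non-significant finding for glucose, HOMA-IR, BP or EDD looks like evidence that no modest effect exists. If power for such effects was really far lower, that inference is unsafe.

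**Working it through.** **Inputs from the protocol article**
- Total N is 16 to 24 (Power analysis and sample size), allocated 1:1 to two arms (Sequence generation), so 8 to 12 per arm.
- There are two measurements, baseline and post-intervention (Primary outcomes).
- The effect size is 0.40 and alpha is 0.05, two-sided.

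**Assumed, because not stated:** pre-post correlation ρ = 0.5.

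**Step 1. Reproduce the stated power.** For the group-by-time interaction with m = 2 measurements, the noncentrality is λ = f²·N·m/(1 − ρ), on 1 and N − 2 degrees of freedom.
- N = 16: λ = 0.16 × 16 × 2/0.5 = 10.24, F(1, 14), power 84.5%.
- N = 24: λ = 0.16 × 24 × 2/0.5 = 15.36, F(1, 22), power 96.3%.

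Both ends match 85–96%. The time main effect with arms pooled gives the same figures, but it does not compare the arms. Other readings that were tried do not match:

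| Reading of 0.40 | N = 16 | N = 24 |
|---|---|---|
| f, interaction, ρ = 0.3 | 71% | 89% |
| f, interaction, ρ = 0.5 | 84.5% | 96.3% |
| f, interaction, ρ = 0.7 | 97% | 99.8% |
| f, between-group main effect, ρ = 0.5 | 41% | 58% |
| f, with λ = f²·N | 32% | 47% |
| f, interaction, three measurements, ρ = 0.5 | 92% | 99% |

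**Step 2. Convert to a difference between arms.** In a 2 × 2 layout, an interaction of f = 0.40 puts each of the four cell means 0.40 outcome SD away from its no-interaction value, with alternating signs. The difference in change between arms is then 4 × 0.40 = 1.6 outcome SD. The SD of change equals the outcome SD × √(2(1 − ρ)), and at ρ = 0.5 the two are equal, so the difference is also 1.6 SD of change.

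As a check, the interaction test is the two-sample t test on change scores, for which λ = (N/4)·d², with d in SDs of change. With d = 1.6, λ = 4 × 2.56 = 10.24 at N = 16 and 6 × 2.56 = 15.36 at N = 24, identical to step 1.

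**Step 3. Power for smaller differences, from the same formula.**

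| Difference in change (SD of change) | λ, N = 16 | Power, N = 16 | λ, N = 24 | Power, N = 24 |
|---|---|---|---|---|
| 0.4 | 0.64 | 12% | 0.96 | 16% |
| 0.8 | 2.56 | 32% | 3.84 | 47% |
| 1.6 | 10.24 | 84.5% | 15.36 | 96.3% |

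The difference detectable with 85% power is 1.61 SD of change with 8 per arm and 1.28 SD with 12 per arm. For 85% power at 0.4 SD of change, about 228 participants would be needed; at 0.8 SD, about 60.

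**Step 4. Dropout.** The stated N is the number enrolled. If two participants were lost (an assumption), leaving 14 or 22 completers, f = 0.40 at ρ = 0.5 gives 78% and 95%.

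**Step 5. Illustration in outcome units.** The documents give no SD of change, so the SDs here are assumed ranges.
- Systolic BP, SD of change 8 to 15 mmHg: a 9 mmHg difference is 1.1 to 0.6 SD, with power 55% to 20% at N = 16 and 75% to 29% at N = 24.
- FMD, SD of change 1.5 to 3 units: a 1-unit difference is 0.67 to 0.33 SD, with power 24% to 10% at N = 16 and 35% to 12% at N = 24.

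**The case against.** The best defence is that nothing was miscalculated. Both ends of the power range reproduce, and the claim is conditional: it covers any outcome whose effect size reaches 0.40, which is true in the metric that gives the figures. A reader might infer an arithmetic error, and the documents do not support that. An article may also leave the metric and the correlation to a fuller protocol, so their absence alone would not be a finding. What remains is that the article itself attaches the word *modest* to a 1.6 SD difference, and without the metric a reader cannot see this.

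A second tempting inference is that the trial misses its own targets. The Introduction says that IMST has been shown to "lower systolic blood pressure (systolic BP) ~9 mmHg in normotensive and hypertensive adults", and it refers to "clinically-meaningful improvements (i.e., >1% unit change" for EDD. The first is a past result in other populations. The second is a threshold for clinical meaning, stated for change before and after training. Neither is a planning value for the arm comparison, and both concern secondary outcomes. The calculations in step 5 are therefore illustrations only.

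The correlation also cuts both ways. A value above 0.5 raises power for the same f, and in outcome-SD units the 1.6 SD of change shrinks to 1.24 at ρ = 0.7 and 1.01 at ρ = 0.8. In SD-of-change units it stays at 1.6.

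Two nearby inconsistencies should not be added to this point. Study design describes an "exploratory clinical trial examining the effects of IMST in 24 adults with T2DM", but 24 is the stated maximum of the 16–24 range. The claim that no effect on glucose has been reported sits awkwardly beside the Discussion, where "another study which was for 12 weeks at a lower resistance of 30% revealed no significant changes in blood glucose levels". Neither changes the power figure.

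Finally, the trial is labelled exploratory, and the Statistical plan already promises effect sizes with confidence intervals. That softens the consequence but does not correct the power statement.

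**Conclusion.** The concern holds as a fault of description. For the arm comparison, 85–96% power at 16–24 participants requires a between-arm difference in change of about 1.6 SD of change. In those units the result does not depend on the correlation or on the effect-size convention. That such a difference is also 1.6 outcome SD, and that it corresponds to f = 0.40, both rest on the assumed correlation of 0.5. At differences of 0.4 to 0.8 SD of change the design has 12–32% power at the minimum size and 16–47% at the maximum. The text thus claims a sensitivity to modest effects that the design does not have. It should be corrected before results are interpreted against it.

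**What to change.** Restate the Power analysis and sample size section as follows.

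- Name 0.40 as Cohen's f for the group-by-time interaction, and state the assumed pre-post correlation of 0.5.
- Delete *modest* and the unqualified *any outcome*.
- Add the detectable difference, for example: *With 8 per arm (minimum) the trial has 85% power for a between-arm difference in change of 1.61 SD of change; with 12 per arm (maximum), 1.28 SD; power for 0.4 SD is 12% and 16%.*
- Express these differences in mg/dL, HOMA-IR units, mmHg and FMD units over a stated range of assumed SDs of change, and say whether N means enrolled or completing participants.
- State that a non-significant result does not exclude modest effects and will be read from the confidence intervals that the Statistical plan already promises.

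The change is to wording only. Sample size, conduct and analysis stay as they are. The cost is that the stated sensitivity becomes less favourable.

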### Recruitment

We will strive to maintain a 1:1 male-to-female ratio within the study groups. Recruitment will be via word of mouth, advertisements placed in area newspapers, social media, and flyers posted around the University of Arizona and to the surrounding local community in Tucson. Interested individuals will be directed to the study website where they will be able to complete a questionnaire to determine their eligibility. Individuals who do not meet the inclusion criteria will be informed of their ineligibility. Candidates that meet eligibility will be contacted for a study overview session.

After the study overview, written informed consent will be obtained in person from each participant before the start of any study-related procedures. Ethical Approval for this study has been obtained from the University of Arizona Institutional Review Board (Protocol 00002239).

## Assignment of interventions

### Sequence generation

The randomization sequence will be created using computer-generated random numbers at a 1:1 ratio in blocks of four. Male and female participants will be randomized using separate randomization tables.

### Allocation concealment mechanism

Group allocation will be stored in an Excel file that is not available to the Research Technician.

### Implementation

Once the Research Technician has completed all enrollment activities for a participant (i.e., a participant has met the inclusion criteria and completed baseline assessments), the Principal Investigator (PI) will inform the research technician of the participant’s allocation group.

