### Interventions

All training will be completed using the POWERbreathe™ K3 trainer (POWERbreathe International Ltd., Warwickshire, U.K.). This is a handheld pressure-threshold device with a computerized threshold sensor. Each participant will be provided with their own device on which they will perform IMST at home, 5 days/week for 6 weeks. They will receive in-person verbal instruction on the training protocol and K3 operation from the Research Technician at the start of the study.

The Research Technician will monitor one training session each week in the CATS facility; the remaining 4 sessions will be completed unsupervised at home. During each visit to the CATS facility, the Research Technician will determine the participant’s PImax and transfer the saved training data from the K3 device to ensure exercises are being completed at home. The PImax will be determined by taking the average of 3 measurements. The Research Technician will then adjust the training resistance as needed to ensure participants are training at the prescribed intensity (i.e., either 15% or 75% of PImax). The participant will then perform a supervised training session. Adherence will be assessed by comparing the quantity and quality of completed training sessions to those prescribed. Monitoring will be conducted using the internal data storage of the POWERbreath™ K3 device. Training session data will be downloaded weekly, prior to supervised sessions, to evaluate participant adherence for the preceding week. Participants also will be required to complete a weekly training log to track any additional exercises outside of the daily IMST training. The safety of the training intervention will be assessed by recording any adverse events reported by the participants. Tolerability will be measured by the rate at which enrolled participants dropped out due to adverse events.

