#### Endothelium dependent dilation

Endothelium Dependent Dilation (EDD) will be assessed via brachial artery flow-mediated dilation (FMD) using high-resolution ultrasonography (Canon Xario 200G), as previously described (34). Participants will be asked to avoid exercise, caffeine, and alcohol for 24 hours, and food for at least 5 hours prior to their visit. FMD will be assessed by measuring the brachial artery diameter and blood velocity at baseline and for 3 minutes following reactive hyperemia which stimulates NO release. Reactive hyperemia is induced by 5 minutes of forearm blood flow occlusion with a cuff placed on the upper forearm and inflated at least 50 mmHg above systolic BP (26, 35). Brachial artery diameter and blood velocity will be analyzed offline using commercially available software (Brachial Analyzer, Medical Imaging Applications LLC, Coralville, IA, USA) (26) and expressed as absolute (mm) and percent change in arterial diameter from baseline (pre-cuff inflation diameter) to post-intervention following the 6 weeks of IMST.

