### Blinding

Due to the nature of the study, the participants are blinded to the intervention.

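### Blocks of four within sex, with past allocations told to the enrolling technician, leave up to about a third of assignments predictable; no masking of FMD reading is stated

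*Protocol article*

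**What the plan says.** - **Sequence (Sequence generation).** The list uses "computer-generated random numbers at a 1:1 ratio in blocks of four". "Male and female participants will be randomized using separate randomization tables". No variation in block length is mentioned.
- **Concealment (Allocation concealment mechanism).** "Group allocation will be stored in an Excel file that is not available to the Research Technician".
- **Disclosure (Implementation).** "Once the Research Technician has completed all enrollment activities for a participant", meaning that eligibility is met and baseline assessments are done, "the Principal Investigator (PI) will inform the research technician of the participant" belongs to.
- **Why the technician must know the arm (Interventions).** "The Research Technician will then adjust the training resistance as needed to ensure participants are training at the prescribed intensity", which is 15% or 75% of PImax.
- **Blinding.** "Due to the nature of the study, the participants are blinded to the intervention". No other role is mentioned.
- **FMD (Endothelium dependent dilation).** "Brachial artery diameter and blood velocity will be analyzed offline". The section names neither the scanner nor the reader, and does not say whether either is masked.
- **Primary outcomes.** Glucose and insulin are assayed by an outside laboratory, and HOMA-IR is calculated from them.

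**The concern.** Concealment has to hold for the next participant, not only for the list as a file. Someone who enrols, learns each past assignment and knows that every block holds two of each arm can work out part of what is coming without opening the file. Disclosure cannot be removed, because the technician sets the resistance. Protection must then come from a sequence that is hard to predict, and a single short block length within sex gives little.

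Two things are at stake.

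- **Selection at entry.** Pre-screening is by phone, and some criteria in Table 1 (an uncontrolled medical condition, unstable clinical disease) leave room for judgement. With 16 to 24 participants, steering two or three could disturb baseline balance. This would reach the primary outcomes too.
- **Observer bias in FMD.** This is a secondary outcome, for which the Introduction sets a change of more than 1% unit as clinically meaningful. Offline analysis makes masked reading feasible, but the text does not provide for it.

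**Working it through.** The plan gives no figure for predictability, so there is none to reproduce. Its only computed design figure is power, and this point does not depend on it.

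**Inputs.** Block length 4, ratio 1:1, separate lists by sex (Sequence generation); 16 to 24 participants (Power analysis and sample size); target sex ratio 1:1 (Recruitment), so 8+8 or 12+12.

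**Step 1: certain assignments in a complete block.** There are six equally likely sequences: AABB, BBAA, ABAB, ABBA, BABA, BAAB. In the first two, the third and fourth assignments are forced. In the other four, only the fourth is.

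- Mean forced per block = (2×2 + 4×1)/6 = 8/6 = 1.333
- Share = 1.333/4 = 33.3%
- For 12+12: six blocks × 1.333 = 8 of 24. For 8+8: four blocks × 1.333 = 5.33 of 16.

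**Step 2: best guess.** Always guessing the arm with more places left in the block gives (0.5 + 0.667 + 0.667 + 1)/4 = 70.8% correct, against 50% by chance.

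**Step 3: incomplete last blocks.** The first two places of a block are never forced; the third is forced with probability 1/3.

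| Total | Split by sex | Expected forced | Share |
|---|---|---|---|
| 16 | 6 + 10 | 1.333 + 2.667 = 4.00 | 25.0% |
| 16 | 7 + 9 | 1.667 + 2.667 = 4.33 | 27.1% |
| 24 | 10 + 14 | 2.667 + 4.000 = 6.67 | 27.8% |
| 24 | 11 + 13 | 3.000 + 4.000 = 7.00 | 29.2% |

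**Step 4: delayed disclosure.** If the immediately preceding same-sex allocation is not yet known, only the fourth place can be certain, and only when the first two match: (1/3)/4 = 8.3%. If two are undisclosed, the share is 0%.

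**Step 5: random blocks of 4 or 6.** Assume equal probability, 12 per sex, and a technician who knows that both sizes are in use but not their order. Exact enumeration, updating the probability of the next arm after each disclosed assignment, gives 6.3% certain and 68.0% best-guess success.

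**Step 6: what the text fixes about assessment.** Table 2 places baseline FMD at Visit 1 and randomisation at Visit 2. The baseline scan is therefore acquired before that participant's allocation exists for the technician. What remains open is the post-intervention scan and the offline reading of both scans.

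**The case against.** The strongest case against has four parts.

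- **One third is a ceiling.** It needs complete blocks, a technician who knows the block length and tracks both lists, and disclosure before every later same-sex enrolment. Inclusion and exclusion are recorded at Visit 1, randomisation comes at Visit 2, and baseline may span 14 days, so overlap between participants is plausible. This stands, and the figure is given as an upper one for that reason. Nothing in the document guarantees overlap, however.
- **Room for selection is limited.** The main gates are numeric (glucose, blood pressure, weight change, duration of stable dose), and the medication criterion is left to the study physician or nurse practitioner. This stands in part, because the clinical-condition criteria and the phone screen still leave some discretion.
- **FMD may well be masked.** A reader might infer that FMD is measured and read unmasked, and that the technician performs the end-intervention tests. The document does not say so. It names the technician for enrolment, PImax, training and data entry, but never for FMD, and an article may leave scan coding to the full protocol. What can be said is that no masking is stated and that the Blinding section stops at participants.
- **Assessor bias hardly touches the main outcomes.** Glucose and insulin come from an outside laboratory, and blood pressure from an automated device. This stands for assessment, but not for selection at entry.

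The document gives no figure from which a size of FMD reading bias could be derived, so none is claimed.

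**Conclusion.** The point holds in a limited form. A single stated block length of four within sex, combined with disclosure of every past allocation to the person who enrols, means that hiding the file does not fully conceal upcoming assignments. The certain share is at most about one third (8 of 24). It is about 25-29% with incomplete last blocks, and about 8% when one same-sex predecessor is undisclosed. All these figures assume that the technician knows the block length and follows the allocations by sex.

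It does not follow that a third of assignments will in fact be known, that selection will occur, or that FMD is assessed unmasked. The FMD part is confined to the absence of any stated masking of the reading, on a secondary outcome. This is a cheap improvement worth making, not a flaw that undermines the trial.

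**What to change.** 1. **Randomisation list.** For participants not yet randomised, generate the male and female lists with block sizes varying at random between 4 and 6, and withhold both the sizes and their order from the technician. Certain assignments fall from 33% to about 6%. Best-guess success falls only from 71% to 68%, so the gain is in removing certainty rather than in preventing guessing. The cost is a new list and a slightly larger possible imbalance within a sex: at most 3 between arms at any moment, when a block of six is open, against 2 with blocks of four.
2. **FMD reading.** Save the clips under random codes that hide arm and time point. Have the existing reader analyse them in random order, and break the code only after all readings are locked. This also remains possible for clips already stored but not yet read. The cost is file renaming, keeping the key away from the reader, and holding results until the lock.
3. **Text.** State in the Blinding section who acquires and who reads the FMD scans, and whether each knows the allocation.

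No extra staff or visits are needed, and the intervention is unchanged.
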